## Abstract

**Background:**

The LUCAS™ device delivers mechanical chest compressions that have been shown in experimental studies to improve perfusion pressures to the brain and heart as well as augmenting cerebral blood flow and end tidal CO_2,_ compared with results from standard manual cardiopulmonary resuscitation (CPR). Two randomised pilot studies in out-of-hospital cardiac arrest patients have not shown improved outcome when compared with manual CPR. There remains evidence from small case series that the device can be potentially beneficial compared with manual chest compressions in specific situations. This multicentre study is designed to evaluate the efficacy and safety of mechanical chest compressions with the LUCAS™ device whilst allowing defibrillation during on-going CPR, and comparing the results with those of conventional resuscitation.

**Methods/design:**

This article describes the design and protocol of the LINC-study which is a randomised controlled multicentre study of 2500 out-of-hospital cardiac arrest patients. The study has been registered at ClinicalTrials.gov (http://clinicaltrials.gov/ct2/show/NCT00609778?term=LINC&rank=1).

**Results:**

Primary endpoint is four-hour survival after successful restoration of spontaneous circulation. The safety aspect is being evaluated by post mortem examinations in 300 patients that may reflect injuries from CPR.

**Conclusion:**

This large multicentre study will contribute to the evaluation of mechanical chest compression in CPR and specifically to the efficacy and safety of the LUCAS™ device when used in association with defibrillation during on-going CPR.

## Background

The LUCAS™ Chest Compression System (Physio-Control/Jolife AB, Lund, Sweden) has been in clinical use since 2003. Experimental data have shown improved perfusion pressures to the brain and heart, enhanced cerebral blood flow and higher end tidal CO_2_ as an indirect measure of cardiac output using the LUCAS™ device as compared with the effects of conventional manual CPR
[1,2]. The LUCAS™ device has also shown higher end tidal CO_2_ values in out-of-hospital cardiac arrest (OHCA) victims compared with manual CPR
[3]. There is some evidence from small case series that the device can be valuable in the catheterisation laboratory to facilitate Percutaneous Coronary Intervention (PCI) during cardiac arrest
[4-6]. The potential benefit of the device has also been reported in special circumstances following accidental hypothermia/drowning and in some cases of in-hospital cardiac arrest
[6-12]. This was recognised by the American and European guidelines for resuscitation in 2010
[13,14].

However, in a cluster randomised pilot study of OHCA patients, a comparison of manual versus mechanical chest compressions with the LUCAS™ device, using the ACLS guideline from 2005, did not show any outcome difference between the groups
[15]. The study was performed in a 2-tier ambulance system with a 6 min delay from the start of treatment to application of LUCAS™ device and a substantial median interval (18 min) from estimated time of cardiac arrest. Defibrillation was not delivered during on-going mechanical chest compressions
[15]. A second randomized pilot study in OHCA victims was performed 2005–2007 in Uppsala and Gävle, Sweden where the LUCAS™ device was used in combination with defibrillation during on-going chest compressions. It showed a trend to an increased return of spontaneous circulation (ROSC) rate (LUCAS = 40% vs. manual = 32%) despite interruptions for rhythm analysis and a median (± SD) of 13.1 ±7.2 min to start of mechanical chest compressions from estimated time of cardiac arrest
[16].

The LINC-study was designed using the knowledge from previous studies, to evaluate the efficacy and safety of mechanical chest compressions using LUCAS™, in association with defibrillation during on-going CPR and with reduced delays. It is powered to detect superiority in four-hour survival of the modified resuscitation algorithm compared with conventional manual resuscitation in patients suffering from OHCA
[13,14].

## Methods and design of the LINC-study

### Ethical approvals and study setting

The LINC-study is being conducted in accordance with regulatory requirements, Good Clinical Practices (GCP), and the ethical principles of the Declaration of Helsinki as adopted by the 18^th^ World Medical Assembly in Helsinki, Finland in 1964. The study was approved by the regional ethical review board in Uppsala, Sweden (Dnr. 2007/271), a research ethics committee in England (Dnr. 08/H0201/33), and the United Human Subjects Research Committees (VCMO) in the Netherlands (Dnr. NL 21034.10008. R-08.10E LINC). The study has been registered at ClinicalTrials.gov (http://clinicaltrials.gov/ct2/show/NCT00609778?term=LINC&rank=1) that supplies information for locating federal and privately supported clinical trials performed around the world.

Jolife AB, Lund, Sweden, the manufacturer of the LUCAS™ device, was the initial sponsor of the study, but since Jolife AB was acquired by Medtronic Inc., Minneapolis MN, USA (March 2011) and thereafter by Physio-Control, Redmond WA, USA the sponsorship was moved accordingly.

There are six participating Emergency Medical Services (EMS) in the LINC-study; Gävle, Malmö, Västerås and Uppsala in Sweden, Utrecht in the Netherlands, and Dorset in England. These centres could fulfill the following requirements: they have earlier experience of pre-hospital studies or in the use of LUCAS™; they are not participating in a clinical study that would be in conflict with the LINC-study; they have responders who are able to defibrillate manually rather than being restricted to the use of Automated External Defibrillators (AEDs); they enjoy good cooperation with their admitting hospitals; their median response interval is relatively brief; the number of patients who could be included was likely to be at least 40 patients/year but not more than 400 patients/year; the hospital to which their patients are admitted are able to perform PCI within 48 h following ROSC; and all surviving patients could be treated with hypothermia following ROSC, regardless of initial ECG rhythm unless contraindicated. Six more EMS was asked to participate but could not fulfill these criteria. Demographic data of the six participating EMS are presented in Table
1.

**Table 1 T1:** Demographic data of the six participating EMS participating in the LINC-study

### Steering committee and contract research organisation (CRO)

The steering committee is monitoring the criteria for termination stated in the study protocol, in which the sponsor reserves the right to discontinue the study before recruitment of the intended number of subjects, but intends to exercise this right only for valid scientific or administrative reasons. These are: unexpectedly high proportion of adverse events; new findings about the investigational product that changes the benefit/risk ratio; the study protocol proves too difficult to achieve; recruitment of eligible subjects is far too slow; critical change in administrative or scientific standards at the sponsor organisation or at the participating organisations; or if the interim analyses show a difference between the groups with a p-value from a two-sided Fisher’s Exact Test of less than 0.005. The study has a steering committee that has the following members:

1. [name] MD PhD, Uppsala, Sweden (principal investigator)

2. [name] MD PhD, Uppsala, Sweden

3. [name] MD, Brighton and Cardiff, UK (advisor during the start-up and manuscript phases only)

4. [name], Borås, Sweden

5. [name] RN, Jolife AB, Lund, Sweden (non-voting) (start-up phase-2008)

6. [name], Jolife AB, Lund, Sweden (non-voting) (from 2008)

7. [name], Director of clinical affairs, Jolife AB, Lund, Sweden (non-voting).

Uppsala Clinical Research Center (UCR), Sweden was appointed CRO to give advice on the outlines of the study, to monitor the study, to give statistical advice, to handle the database, and to perform the statistical analyses of the results. This will be done in accordance with GCP for clinical trials.

### Eligibility criteria for the study

Eligible patients for the LINC-study are adults with an unexpected OHCA for whom an attempt of resuscitation is considered appropriate.

The exclusion criteria are:

1. Traumatic cardiac arrest, including hanging

2. Age believed to be less than 18 years (no upper limit)

3. Known pregnancy

4. Defibrillated before LUCAS™ is brought to the scene

5. Patients body size not fitting the LUCAS™ System

### Study enrolment and randomisation

The device is brought to all patients with dispatch codes for sudden cardiac arrest, loss of consciousness, or other local guidelines suggesting OHCA. Enrolment into the study is at the time that paramedics recognise the situation as a cardiac arrest after they arrive on scene. After confirmation of the arrest, one ambulance professional immediately starts manual CPR while another takes care of the randomisation procedure. All patients fulfilling the inclusion criteria and having no known exclusion criteria are randomised using block randomisation with site (EMS) as stratification variable. Block size is set to 6, but has been kept unknown to all personnel involved throughout the study. Randomisation is at the patient’s side by opening an envelope which is enclosed in the LUCAS™ back pack. Inside the envelope there will be a note prompting either conventional manual or LUCAS™ CPR. A replacement envelope from the block of 6 is added to the LUCAS pack after each use.

Patients suffering a cardiac arrest witnessed by the ambulance crew are handled according to a separate algorithm and if eligible they are randomized into the study (Figure
1).

**Figure 1 F1:**
[figure not shown]
The separate algorithm used for patients suffering a cardiac arrest witnessed by the ambulance crew and used for these witnessed cases for eligible judgment and randomisation into the LINC-study.

### Study algorithms and post-resuscitation care

Ventilation and the dosages of drugs in both groups are given according to the International Consensus 2005 as adopted by the European Resuscitation Council
[13].

### The LUCAS™ algorithm

Patients randomised to LUCAS™ CPR are treated initially with manual compressions with minimised interruptions until the device is unpacked and ready to use. LUCAS™ is attached to the patient as soon as possible. In this group the defibrillator must be in manual mode. Mechanical compressions are continued initially for 3 min without checking heart rhythm, irrespective of any manual compressions that have been given by bystanders. The sequence is not interrupted for a shock that is delivered during compressions after 90 seconds of this first 3 min cycle, with the remaining 90 seconds of continued compressions to follow. Thus, the first shock is given on the basis only of definite cardiac arrest without knowledge of whether it is or is not ‘shockable’. Subsequently, heart rhythm is determined after each 3 min cycle by interrupting mechanical compressions briefly and never for longer than 10 seconds. If the analysed rhythm is shockable, a new 3 min cycle of compressions is started, incorporating as before one shock delivered after 90 seconds of on-going compressions. If the rhythm is not shockable, a 3 min cycle of compressions without any shock is followed by a new rhythm analysis. Heart rhythm and circulation are checked after each 3 min cycle (Figure
2).

**Figure 2 F2:**
[figure not shown]
The LUCAS algorithm used in the LINC-study.

### The conventional manual CPR algorithm

Those randomised to conventional manual CPR are treated in accordance with the International Consensus 2005 as adopted by the European Resuscitation Council
[13] (Figure
3).

**Figure 3 F3:**
[figure not shown]
The adult ALS algorithm used as control in the LINC-study.

### Post resuscitation care

If the patient achieves ROSC, he/she should be treated with mild hypothermia to 32–34 degrees Celsius for 24 h, regardless of initial ECG rhythm, unless contraindications exist. Acute coronary angiography should be considered during the first 48 h of hospital admission.

### Mechanical chest compression devices

Two models of LUCAS have been used during the study. Initially, from January 2008 to early 2010, it was the LUCAS™ 1 Chest Compression System which was a pneumatic gas-driven device. From early 2010, this was replaced by the LUCAS™ 2 Chest Compression System which is powered electrically. Both devices achieve mechanical chest compressions at a constant rate of 100 per minute and to a fixed depth of 4–5 cm by a piston that has a 50% duty cycle, with the added feature of a suction cup that may assist the chest back to neutral position. The LUCAS™ 1 and LUCAS™ 2 devices used in the study both adhere with the 2005 international guidelines on resuscitation
[13,14,17,18].

### Patient consent

The nature of the study, in relation to patients who are unconscious, precludes consent before enrolment. It is the responsibility of the investigator to provide, for each surviving subject with mental capacity, full and adequate verbal and written information about the objectives and procedures of the study. They are given the opportunity to ask questions and to decide whether or not they are willing for their results to be included in the dataset. They are also told of their freedom to withdraw from the study at any time and that withdrawal will not affect their future medical care. In cases where the subjects survive without having the mental capacity to accept or withdraw participation, written information is presented to the family, who then take the decision to continue participation or not. Subjects included who do not survive will stay in the study; the family will not be asked for consent. This prevents any positive bias in the results.

### Efficacy and safety evaluation in the study

For efficacy evaluation the following primary and secondary endpoints that will be analysed in the study are:

1. Primary endpoint

a. Four-hour survival after successful restoration of spontaneous circulation (ROSC).

2. Secondary endpoints

a. Restoration of spontaneous circulation defined as a spontaneous palpable pulse.

b. Arrival to the emergency room with spontaneous palpable pulse.

c. Survival to discharge from ICU without severe neurological impairment (CPC 1 or 2).

d. Survival to hospital discharge without severe neurological impairment (CPC 1 or 2).

e. Survival 1 and 6 months after cardiac arrest without severe neurological impairment (CPC 1 or 2).

The safety evaluation in the study comprises three main areas. The first relates to serious adverse events or serious adverse device events. These cover events directly related to CPR, as judged by investigator/co-investigator, and assumed to occur after the randomisation in the study with any of the following sequelae: death; serious deterioration of health in patient; life threatening illness or injury, permanent deterioration of body function or structure; prolongation of hospitalisation; conditions that require medical or surgical treatment to prevent any of the foregoing.

The second area for safety evaluation is any post mortem examination that may reflect injuries from CPR. For comparison of injuries from the two different CPR techniques, autopsies are performed to quantify the number of injuries possibly affecting survival. They are undertaken in three centres (Uppsala, Gävle, and Västerås in Sweden). The aim is to obtain autopsy results from a total of 300 study patients with 150 who have received manual chest compressions only and 150 after LUCAS™ chest compressions.

The third area relates to the criteria for termination of the study stated in the protocol (described above) that would be considered by the steering committee, sponsor, and the independent safety committee within the Scandinavian Society of Anaesthesiology and Intensive Care Medicine research group (SSAI).

### Sample size and statistical methods

Considerations for the sample size calculations are based upon data from the Uppsala-Gävle pilot study,
[15] together with data from the National Registry of Cardiac Arrest in Sweden
[19]. It was assumed that in the conventional manual treatment group, the proportion of four-hour survival will be 25% and in the LUCAS-CPR treatment group the proportion of four hour survival will be at least 31%. To detect the anticipated difference of at least 6% with a power of 90% in the final analysis, the study requires a total of 2500 patients, i.e. 1250 patients in each treatment group in the intention to treat population. For the intention to treat and predefined populations the primary and all secondary endpoints will be compared between treatment groups with frequency tables and two-sided Fisher’s Exact Tests at the 4.8% and 5% level, respectively; 95% confidence intervals for difference in proportions will be presented where applicable. The result for the primary endpoint in the intention to treat population is confirmative while the other results are regarded as supportive.

Injuries after CPR will be studied in detail. The proportions of patients will be compared between the two treatment groups with frequency tables and two-sided Fisher’s Exact Test at 5% level.

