### Analysis populations

The analysis populations are defined as:

Safety population: all randomised patients except surviving patients without informed consent. Intention to treat (ITT) population: all randomised patients except surviving patients without informed consent. Predefined population (PP): all randomised patients, except surviving patients without informed consent, who have completed the study treatment without any protocol violations. Possible protocol violations are:

• Inclusion criterion not fulfilled.

• Primary exclusion criteria subsequently confirmed to have been present.

• Dispatch time to ambulance stop at the address exceeding 12 min.

• Cardiac arrest not witnessed by sight or sound (If data are missing regarding whether the cardiac arrest was witnessed or not, the patient should be regarded as not witnessed).

• LUCAS™ Chest Compression System not brought to the patient or no record form filled in.

If the actual treatment given is not that to which the patient was randomised, the patient will be included in the ITT population set as randomised, but in the PP population according to the actual treatment.

For missing data, the primary endpoint and the first four of the secondary endpoints will be defined according to the worst case principle, i.e. as failures in the ITT population. The confirmative analysis will be performed in the ITT population. The PP analysis will be regarded as supportive. In the PP analysis no imputation of missing values will be performed.

An interim analysis of the primary endpoint was performed during spring 2011 by an independent safety committee within the Scandinavian Society of Anaesthesiology and Intensive Care Medicine research group (SSAI). This was done according to protocol, after 1500 patients had been randomized, using the primary endpoint i.e. 4 h of ROSC, and performed on the intention to treat population. In the interim analysis the criterion for terminating the study is that the p-value from a two-sided Fisher’s Exact Test is less than 0.005. A group-sequential analysis plan
[20] is used to preserve a Type I error of at most 5%, so that after completion of the study the primary hypothesis will be tested at a level of 4.8%.

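### The confirmatory Fisher test ignores the site stratification of the randomisation: it is valid and adequately powered, but conservative, at a cost of about one point of power at the design effect

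*Protocol article*

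**What the plan says.** The protocol article, under *Study enrolment and randomisation*, allocates patients by "block randomisation with site (EMS) as stratification variable", in blocks of 6. The section *Ethical approvals and study setting* gives the number of strata: "There are six participating Emergency Medical Services (EMS) in the LINC-study", spread over Sweden, the Netherlands and England.

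Under *Sample size and statistical methods*, "the primary and all secondary endpoints will be compared between treatment groups with frequency tables". The tests and their levels are named next: "two-sided Fisher’s Exact Tests at the 4.8% and 5% level, respectively". The 4.8% applies to the intention-to-treat population, where the primary endpoint is the only confirmatory result. Site has no part in that test. The same section promises 90% power for 25% against 31% four-hour survival with 1250 patients per arm, and 95% confidence intervals for differences in proportions.

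Under *Analysis populations*, the interim analysis after 1500 patients also used Fisher's test: "the criterion for terminating the study is that the p-value from a two-sided Fisher’s Exact Test is less than 0.005". The final level of 4.8% follows from that look.

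**The concern.** Blocks within site keep the two arms balanced at every site, so differences in survival between sites contribute almost nothing to the true variance of the treatment difference. A single pooled 2x2 table still counts those differences in the variance it estimates. If sites differ in survival, the pooled test therefore uses too large a standard error. Fisher's conditioning adds a second layer of conservatism, which is present even when all sites are alike.

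What is at stake is efficiency. The test spends less than the 4.8% it is allowed, so it detects a true effect slightly less often than the same data permit. The loss grows if the true effect is below the planned 6 points. The documents also state the test, its level and its confirmatory status outright, so this is a choice the article has made and not a detail left to the analysis plan.

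**Working it through.** **Inputs from the protocol article:** 25% and 31% four-hour survival, 1250 per arm, two-sided 4.8% at the final analysis, interim at 1500 of 2500 with p < 0.005, six sites, 1:1 within site. **Assumed:** the site-specific survival rates, which the text at hand does not give. The ranges used are all sites equal, 18% to 32%, and 12% to 38%, each averaging 25%.

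**1. The plan's own sample size.** With z = 1.977 (two-sided 4.8%), z = 1.282 (90% power) and mean rate 0.28:

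n = [1.977·√(2·0.28·0.72) + 1.282·√(0.25·0.75 + 0.31·0.69)]² / 0.06² ≈ 1188 per arm (2376 in total).

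With the continuity correction that mimics Fisher's test:

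n_c = (n/4)·[1 + √(1 + 4/(n·0.06))]² ≈ 1221 per arm (2442 in total).

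The stated 2500 is within 3% of 2442. Exact enumeration of Fisher's test at 1250 per arm gives 90.7% power (uncorrected chi-square: 91.4%). The planned size therefore already covers Fisher's conservatism.

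**2. Conservatism from Fisher's test itself.** Under the null at 25%, SE = √(2·0.1875/1250) = 0.0173. The correction is about 1/1250 = 0.0008, or 0.0008/0.0173 = 0.046 on the z scale. The effective critical value is 1.977 + 0.046 = 2.023, a two-sided size of about 4.3%. Exact enumeration also gives 4.3%.

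**3. Conservatism from ignoring site.** The pooled variance is 0.25·0.75 = 0.1875 per patient. The within-site variance is this minus the variance of the site rates. For k equally spaced rates at spacing d, that variance is d²(k² − 1)/12.

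- 18% to 32%: d = 0.028, variance 0.028²·35/12 = 0.0023. SE ratio √(0.1875/0.1852) = 1.006.
- 12% to 38%: d = 0.052, variance 0.052²·35/12 = 0.0079. SE ratio √(0.1875/0.1796) = 1.022.

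A pooled confidence interval is thus about 0.6% or 2.2% too wide. For 12% to 38%, both effects together give a critical value of 2.023·1.022 = 2.068, a size of about 3.9%. Simulation gives 3.8% to 3.9%.

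**4. Power.** Simulation used 200,000 trials per scenario, near-equal sites, exact Fisher p-values, CMH without continuity correction, and a 4.8% level. The overall difference was held at the stated value.

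| Assumed site control rates | Real size, Fisher / CMH | Power at 6 points, Fisher / CMH | At 5 points | At 4 points |
|---|---|---|---|---|
| all 25% | 4.3% / 4.8% | 90.7% / 91.4% | 78.3% / 79.6% | 59.3% / 61.1% |
| 18% to 32% | 4.2% / 4.8% | 90.8% / 91.7% | 78.4% / 80.0% | 59.2% / 61.5% |
| 12% to 38% | 3.8–3.9% / 4.8% | 91.3% / 92.6% | 78.7% / 81.2% | 59.6% / 63.1% |

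Repeat runs with other seeds or site shares of 10% to 25% moved sizes by at most about 0.2 points and powers by about 0.3. Widening the spread to 9% to 42% gave a gap of 1.7 points at 6 points (91.5% against 93.2%).

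**5. Type I error if the final test becomes CMH.** With correlation √(1500/2500) between the looks, interim p < 0.005 and final 4.8%, the normal approximation gives an overall two-sided error of 4.93%. This is still within the article's limit of 5%.

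**The case against.** The strongest objection is that nothing promised is missed. The sample size matches a Fisher-type calculation, and the named test at the named level delivers slightly more than 90% power. Its error lies on the safe side, consistent with the article's aim of at most 5%. All of this stands.

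A reader might infer that the trial is underpowered. For instance, a simulation with sites at 12% to 38% and a fixed odds ratio of 1.35 puts Fisher's power at about 88% to 89%. The documents do not support that reading. An odds ratio of 1.35 at those sites gives an overall difference of only 5.7 points (25.0% against 30.7%), so the drop comes from a smaller effect and not from the test. With the difference held at the planned 6 points, Fisher's power stays above 90% in every scenario run. Nor is there inflation of type I error, and with 1:1 allocation within site the pooled difference is not biased.

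A reader might also fault the absence of adjustment for witnessed status or response interval. A supportive covariate model is commonly left to the analysis plan, and the documents give no figures from which to size its gain. It is not part of this point.

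Timing is a fair objection. The interim analysis was done with Fisher's test in spring 2011, and enrolment closed at the end of August 2012. A change of confirmatory test that late could look chosen after the fact. This calls for a dated, documented change made before unblinding, but it does not defeat the change: the interim decision and both levels stay as they were.

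**Conclusion.** The point holds as a minor efficiency and coherence correction. The randomisation is stratified by site, the confirmatory test is not, and that test is conservative. Of the loss at the design effect, about 0.7 points come from Fisher's test itself and up to roughly another point from ignoring site.

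The part due to Fisher's test follows from the article's own figures. The part due to site rests on assumed site rates and would vanish if survival were the same at every site. In every scenario tested CMH held its level and was more powerful than Fisher's test. Because allocation is 1:1 within site, the estimate itself would hardly change. The gain is in the test and, if sites differ, in the width of the interval.

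**What to change.** Before unblinding, make the confirmatory intention-to-treat test of four-hour survival a CMH test stratified by EMS, two-sided at the same 4.8% level, without continuity correction. Report a Mantel-Haenszel risk difference over the six sites with its confidence interval. Keep the unstratified Fisher test, as used at the interim, as a named sensitivity analysis.

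The cost is a change of wording in the protocol and analysis plan. It needs no extra patients or data, since site is known for every patient. The interim threshold of 0.005 and the final level stay unchanged. The downside is a change of confirmatory test after a Fisher-based interim, so it should be dated, should state that no unblinded results informed it, and should be disclosed in the report. If the arms have already been compared, Fisher's test should stay confirmatory and the CMH result should be reported as supportive.

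### The confirmatory ITT test is an unadjusted Fisher's exact test although site, witnessed status and dispatch-to-stop time are at hand: a small missed gain in precision, not an error

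*Protocol article*

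**What the plan says.** Under Sample size and statistical methods, the article fixes the analysis: "the primary and all secondary endpoints will be compared between treatment groups with frequency tables and two-sided Fisher’s Exact Tests". For the ITT population the level is 4.8%. It adds that "The result for the primary endpoint in the intention to treat population is confirmative while the other results are regarded as supportive". No covariate or stratification factor enters the comparison.

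Three pre-randomisation variables appear elsewhere:

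- Site is the stratification variable (Study enrolment and randomisation).
- Two items on the list of protocol violations under Analysis populations are "Dispatch time to ambulance stop at the address exceeding 12 min" and "Cardiac arrest not witnessed by sight or sound". They serve only to remove patients from the supportive predefined population. Missing witnessed status is counted there as not witnessed.

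On size, the plan wants 90% power for a 6-point difference and concludes that "the study requires a total of 2500 patients, i.e. 1250 patients in each treatment group in the intention to treat population". The assumed rates are 25% and 31%.

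**The concern.** Membership of the predefined population cannot be assigned without witnessed status and dispatch-to-stop time, so both have to be collected. Both are settled before the envelope is opened at the patient's side. If they predict four-hour survival, a crude two-by-two table leaves their share of outcome variation in the error term. Randomisation balances only site by design, so chance imbalance in the other two also goes uncorrected.

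An adjusted analysis can target the same quantity, the marginal ITT difference in proportions, and report it with a narrower interval. At stake is precision at a fixed 2500 patients. Validity is not at stake.

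**Working it through.** **Inputs from the article.** Survival 25% vs 31%; 1250 per arm; final two-sided level 0.048 (z = 1.9774); interim after 1500 of 2500 patients (information fraction 0.6) with boundary p < 0.005 (z = 2.8070). Not in the article: R², the share of outcome variance that the covariates explain. It is assumed below.

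**1. The plan's own figure.** With mean rate 0.28,

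n per arm = [1.9774·√(2·0.28·0.72) + 1.2816·√(0.25·0.75 + 0.31·0.69)]² / 0.06² = 1188 rounded up.

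The continuity correction that approximates Fisher's test gives 1221 per arm, 2442 in total, within 3% of 2500. Full enumeration of Fisher's test at 1250 per arm and 0.048 gives power 90.7%, and actual size 4.3% when both rates are 25%. The stated sample size and power therefore hold without adjustment.

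**2. Unadjusted reference.** SE of the risk difference = √[(0.25·0.75 + 0.31·0.69)/1250] = 0.01792. Power ≈ Φ(0.06/0.01792 − 1.9774) = Φ(1.371) = 91.5%. The 95% half-width is 1.96 × 0.01792 = 3.51 points.

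**3. Range for R².** Assume 70% witnessed, overall survival 28%, mean response time 8 minutes (gamma-distributed), and R² = variance of the predicted risks / (0.28·0.72). Witnessed-vs-not odds ratio and odds ratio per minute:

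- 1.5 and 0.95 give R² = 0.014
- 2 and 0.93 give R² = 0.03
- 3 and 0.90 give R² = 0.065

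I take 0.10 as an upper end. Any contribution from site is not counted.

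**4. Gain.** Adjustment multiplies the variance by about (1 − R²), so power ≈ Φ(0.06/(0.01792·√(1 − R²)) − 1.9774), and the equivalent unadjusted N is 2500/(1 − R²).

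| R² | Power | 95% half-width (points) | Equivalent N |
|---|---|---|---|
| 0 | 91.5% | 3.51 | 2500 |
| 0.014 | 91.8% | 3.49 | 2535 |
| 0.03 | 92.3% | 3.46 | 2577 |
| 0.065 | 93.1% | 3.40 | 2674 |
| 0.10 | 94.0% | 3.33 | 2778 |

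**5. Type I error with the interim already done by Fisher's test.** The unadjusted interim statistic and an adjusted final statistic have correlation √(0.6·(1 − R²)). With boundaries 2.8070 and 1.9774, overall two-sided alpha is 0.0493 at R² = 0, 0.0494 at 0.03 and 0.0497 at 0.10. The 4.8% final level can stay.

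**The case against.** The strongest reply is that nothing is wrong. The test is valid, the sample size reproduces, and the target power is met. A preference for an adjusted estimate is a preference for efficiency. That stands, and it sets the weight of this point.

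A reader might infer more in two ways.

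- **A larger gain.** Setting the adjusted power against Fisher's 90.7% and crediting the whole gap to the covariates overstates them. Enumeration of an unadjusted z-test at 4.8% already gives 91.4%, so about 0.7 point comes only from leaving a conservative exact test. The covariates themselves add about 0.4 to 2.5 points. Even that is conditional, because the article nowhere states how prognostic they are; it lists them as protocol violations, not as predictors.
- **A free gain.** No new data are needed, but there are costs. The interim was run in spring 2011 and the last patient enrolled at the end of August 2012, so replacing the confirmatory test now needs evidence that it was decided blind to outcome. The rule for missing witnessed status is given only for the predefined population, and record forms may be absent. For crew-witnessed arrests, which can be randomised, dispatch-to-stop time is not a delay after collapse. Witnessed status may also be written down by crews who already know the allocation.

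The crew-witnessed problem weakens prediction but does not bias a standardised estimate under randomisation. Recording after allocation is a genuine reservation about witnessed status, and a second analysis without it answers it. An unseen SAP may contain supportive adjusted analyses. The choice of confirmatory test, however, is fixed in the article itself.

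**Conclusion.** The point holds as a low-severity efficiency suggestion. The confirmatory test leaves out the randomisation stratifier and two baseline variables that the trial has to record. For an assumed R² of 0.014 to 0.10, adjustment would raise power from about 91.5% to 91.8–94.0%, equal to roughly 35 to 280 extra patients, and narrow the half-width by at most about 0.2 point. That would rarely change a conclusion. The result rests on the assumed R² and a normal approximation. The article does not support calling the planned test invalid or the trial underpowered.

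**What to change.** Before unblinding, amend Sample size and statistical methods so that the confirmatory ITT analysis is a covariate-adjusted risk difference. Fit a logistic model, standardise it to the whole ITT population, use a robust standard error, and test at 4.8%. Include:

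- treatment and site;
- witnessed status, with crew-witnessed as its own category, and missing counted as not witnessed by extending the existing rule to the ITT population;
- dispatch-to-stop time, set to a constant for crew-witnessed arrests, with a simple stated rule for missing times.

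Keep Fisher's test as the unadjusted check. Also report a version adjusted for site and dispatch-to-stop time only, in case knowledge of the allocation affected how witnessed status was recorded. State that the pre-shock rhythm described in the Discussion is not a covariate, because in the LUCAS arm it is inferred from the state after the first shock.

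The cost is a short amendment plus a dated record that it was made blind to outcome after the interim. The test becomes large-sample rather than exact, which matters little with about 700 events expected (0.28 × 2500). If outcomes have already been unblinded by arm, the adjusted analysis should be supportive only.
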